### Outcome measures

#### Recruitment, retention and data completeness

Participants will be deemed to have been fully retained in the study if (a) they do not contact the study team to withdraw or unsubscribe and (b) if psychosocial questionnaires sent at T1 and T2 are completed. Partial retention rates for those who only complete the questionnaire at T1 or who only contribute food purchase data will also be calculated. Recruitment and retention rates from different socioeconomic groups (measured by area-level deprivation) will be assessed by comparison of the socioeconomic profile of the recruited sample with the profile of the whole loyalty card database from which the sample was drawn.

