**Methods/design:**

The objectives of this two-arm randomised controlled pilot trial are to assess recruitment, retention and data completion rates, to generate potential effect size estimates to inform sample size calculations for the main trial and to assess the feasibility of conducting such a trial. Participants will be recruited by email from a loyalty card database of a UK supermarket chain. Eligible participants will be over 18 and regular shoppers who frequently purchase ready meals or pizzas. The intervention is informed by a review of previous interventions encouraging the use of nutrition labelling and the broader behaviour change literature. It is designed to impact on mechanisms affecting belief and behavioural intention formation as well as those associated with planning and goal setting and the adoption and maintenance of the behaviour of interest, namely traffic light label use during purchases of ready meals and pizzas. Data will be collected using electronic sales data via supermarket loyalty cards and web-based questionnaires and will be used to estimate the effect of the intervention on the nutrition profile of purchased ready meals and pizzas and the behavioural mechanisms associated with label use. Data collection will take place over 48 weeks. A process evaluation including semi-structured interviews and web analytics will be conducted to assess feasibility of a full trial.

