### Participants

Participants will be recruited from the database of loyalty card holders held by the participating supermarket chain. This database contains approximately 1.1 million people. Where a loyalty card is shared by multiple users, only one user will be contacted for recruitment. The exclusion criteria are shown in Fig. 2. The recruitment email will only be sent to loyalty card holders who meet inclusion criteria 1, 2, 3 and 4. Eligibility for the three remaining criteria will be assessed using responses to the screening questionnaire. Inclusion criterion 4 requires participants to regularly shop at large supermarkets—this is to ensure that they have access to a wide range of ready meals and pizzas.

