### Statistical analysis

Demographic characteristics and outcomes data will be summarised with counts and percentages for categorical variables, means (standard deviations) for normally distributed continuous variables and medians (with interquartile or simple ranges) for other continuous variables. At time points T1 and T2, repeated measures ANCOVA will be used to assess differences between intervention and control arms, adjusted for gender, dependent children and baseline measures [26]. If outcome data are not normally distributed, then differences will be assessed either using transformed data or by using appropriate non-parametric tests. Results will be presented as point estimates accompanied by 95 % confidence intervals. Analyses will be conducted on an ‘intention to treat’ basis (i.e. data for participants who unsubscribe from the study will be used in the final analyses). Subgroup analyses by socioeconomic status will be conducted to assess potential impact of the intervention on social inequalities. Since this is a pilot study with a sample size based on a small effect size and unclear recruitment rates, it is not guaranteed that the study will be adequately powered to detect differences between intervention and control arms, particularly in sub-analyses. The socioeconomic status of the participants will be compared with that of the loyalty card database from which they are drawn to assess inequalities in recruitment, using area-level deprivation measures.

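### Socioeconomic inequality in recruitment is judged against the whole loyalty card database although only pre-screened holders are emailed, so eligibility and response may be confounded; the same comparison cannot show retention at all

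*Protocol article*

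**What the plan says.** Three places in the protocol article bear on this.

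- **Outcome measures, Recruitment, retention and data completeness.** The method for both rates is a single comparison: "Recruitment and retention rates from different socioeconomic groups (measured by area-level deprivation) will be assessed by comparison", the comparison being the "comparison of the socioeconomic profile of the recruited sample with the profile of the whole loyalty card database from which the sample was drawn".
- **Statistical analysis.** The comparator is repeated, for recruitment only. The participants' socioeconomic status is to be "compared with that of the loyalty card database from which they are drawn to assess inequalities in recruitment".
- **Participants.** On the database: "This database contains approximately 1.1 million people". On who is invited: "The recruitment email will only be sent to loyalty card holders who meet inclusion criteria 1, 2, 3 and 4". On the rest: "Eligibility for the three remaining criteria will be assessed using responses to the screening questionnaire". One of the criteria applied before the email is described: "Inclusion criterion 4 requires participants to regularly shop at large supermarkets".

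The abstract describes the target population: "Eligible participants will be over 18 and regular shoppers who frequently purchase ready meals or pizzas". The Recruitment and allocation strategy section says that emailed holders are selected at random. Read with the Participants section, that random selection is made among holders who pass criteria 1 to 4.

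**The concern.** The database is not the population that is invited. Recruits pass through three steps: criteria 1 to 4 (applied by the supermarket before any email), response to the email, and criteria 5 to 7 (applied by questionnaire). Only the second step is what is ordinarily meant by inequality in recruitment. A comparison of recruits with the whole database reflects all three.

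The eligibility rules concern shopping habits, such as regular use of large stores and frequent purchase of ready meals or pizzas. It is plausible that these vary with area deprivation. If they do, a difference produced by the rules could be read as unequal willingness to take part, or an offsetting difference could conceal unequal willingness. Either reading could mislead those who plan recruitment to the full trial.

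Retention is a separate matter. It concerns what happens after enrolment, and the profile of those enrolled says nothing about it.

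**Working it through.** **1. The article's own recruitment denominator.** Inputs are the assumed rates in Recruitment and allocation strategy and the totals that follow them: recruitment 5%, loss of 20% of consenting participants on criteria 5 to 7, 33,000 emails, about 1300 recruits.

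- Forward: 33,000 × 0.05 × 0.80 = 1320, against about 1300 stated.
- Backward: 1300 / (0.05 × 0.80) = 32,500 emails, against 33,000 stated.

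The plan's figures reproduce. They also show that overall recruitment is counted per emailed holder. Emailed holders are 33,000 / 1,100,000 = 3% of the database. The socioeconomic assessment uses the other denominator, the full 1.1 million.

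**2. What the planned comparison estimates.** For the most deprived band relative to the rest, let E be the ratio of the proportions meeting criteria 1 to 4, R the ratio of response among those emailed, and S the ratio of passing criteria 5 to 7 among those who respond. Then:

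- recruits against the whole database: E × R × S
- enrolled/emailed: R × S
- consenting/emailed: R

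Only the last isolates response. The planned comparison equals R only when E × S = 1.

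**3. Illustration of size.** The documents give no deprivation profile, so every input here except n = 1300 is an assumption: 20% of the database lies in the most deprived fifth, R = 1 and S = 1 (no inequality in response or in screening), and the database share is treated as known. The recruited share is 0.2E / (0.2E + 0.8). The standard error under a 20% share is √(0.2 × 0.8 / 1300) = 1.11 percentage points.

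| E (assumed) | Recruited share | Apparent ratio against database | Standard errors from 20% | Ratio against emailed holders |
|---|---|---|---|---|
| 0.5 | 11.1% | 0.5 | −8.0 | 1.0 |
| 0.8 | 16.7% | 0.8 | −3.0 | 1.0 |
| 0.9 | 18.4% | 0.9 | −1.5 | 1.0 |
| 1.0 | 20.0% | 1.0 | 0 | 1.0 |
| 1.25 | 23.8% | 1.25 | 3.4 | 1.0 |
| 1.5 | 27.3% | 1.5 | 6.6 | 1.0 |

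For example, E = 0.8 gives 0.16 / 0.96 = 16.7%, and (16.7 − 20.0) / 1.11 = −3.0.

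**4. Masking.** With R = 0.7 (a real shortfall in response), E = 1.43 and S = 1, the apparent ratio is 1.43 × 0.7 = 1.0. The inequality disappears from the planned comparison.

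**5. Retention.** No assumption is needed. Hold the recruited sample and the database fixed. Retention in the most deprived band could be anything from 0% to 100%, and the comparison of recruits with the database would not change.

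**The case against.** The strongest points on the other side are these.

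- **The distortion is conditional.** A reader might infer that the trial will report eligibility differences as recruitment inequality. The documents do not support that. They give no deprivation profile and no association between eligibility and deprivation, and with E × S = 1 the distortion is nil. The criteria are listed in a figure that is not reproduced in the text reviewed. Only criterion 4 is described as a filter before the email, and the text does not say whether the ready meal and pizza condition is applied before or after it. This objection stands, and the point is put as a possibility.
- **The whole-database comparison answers a fair question.** The Discussion looks ahead to roll-out to a wider population, for which total selection, eligibility and response together, is of interest. This stands too. What fails is its use as a measure of recruitment rates and of inequality in recruitment.
- **The retention wording may be compression.** Full and partial retention are defined in the same paragraph, and a breakdown by deprivation band can be made from data the team will hold. That makes the correction easy, but the only method stated for retention by socioeconomic group still cannot deliver it.
- **The stakes are limited.** The first study objective asks for reliable recruitment and retention estimates without mentioning socioeconomic groups, so a reader should not infer that this objective as a whole is undermined. This stands.

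**Conclusion.** The point holds in a limited form. The stated comparator does not match the recruitment design and cannot separate eligibility from response. It may therefore show an inequality in recruitment that does not exist or hide one that does. Whether it does so, in which direction and by how much depends on how eligibility varies with deprivation, which the documents leave unquantified. On the assumptions above, eligibility ratios of 0.8 or 1.25 would be enough for an apparent difference of at least 3 standard errors, 0.9 would give about 1.5, and 1.0 none.

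The retention part is firmer: as written, the comparison is uninformative about retention by group, whatever the eligibility pattern.

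The consequence is confined to the socioeconomic feasibility description. The comparison of intervention with control, the overall recruitment and retention rates, and the inputs to the main-trial sample size are not affected. The change should be made, but it does not threaten the trial.

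**What to change.** Amend Recruitment, retention and data completeness, and the matching sentence in Statistical analysis, as follows.

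1. Make emailed holders the comparator for recruitment.
2. Report by area-deprivation band:
   - consenting/emailed (response);
   - losses on criteria 5, 6 and 7 among those who consent;
   - enrolled/emailed (the net recruitment rate);
   - retained/randomised, using the full and partial definitions already given.
3. Keep recruits against the whole database only as a description of how representative the sample is of all card holders. If the effect of criteria 1 to 4 is of interest, compare emailed holders with the database.

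The separate line for losses on criteria 5 to 7 is needed because enrolled/emailed on its own still mixes response with later ineligibility, and the article expects those criteria to remove 20% of consenting participants.

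The cost is one aggregate count of emailed holders by deprivation band from the supermarket, which sends the emails, plus the change of wording. The retention breakdown uses data the research team will already hold. Nothing in the design, the randomisation or the analysis between arms changes.

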#### Effect sizes

The research team will receive electronic sales data for all food purchases during the study period from the participating supermarket at two stages: after allocation and after completion of the study. The primary outcome measures for the main trial will be healthiness of ready meals and pizzas that carry traffic light labelling. For each participant, mean healthiness of all ready meals and pizzas purchased during the entire time period will be assessed in T-1, T1 and T2 and differences between intervention and control arms at T1 and T2 will be controlled for differences at baseline (T-1). Purchase data will be collected via electronic sales data linked to participants’ loyalty cards. Comparisons between intervention and control at T1 will measure the immediate effect of the intervention, and at T2 will measure whether the effect is sustained for the following 12 weeks after the intervention is removed. The ‘healthiness’ of each purchased ready meal or pizza will be a combination of the information provided on the traffic light label, weighted by factors derived from a parallel choice experiment assessing the importance of different elements of the label (manuscript under preparation). Details of how the scale is constructed are provided in the appendix.

Secondary outcome measures (assessed as difference in means and SD between intervention and control) will beNumber of ready meals and pizzas purchased in T2/T1.Amount (£) of ready meals and pizzas purchased in T2/T1.Total amount (g) of fat, saturated fat, sugar and salt in ready meals purchased in T2/T1.Amount (£) of all foods purchased in T2/T1.Amount (£) of fruit and vegetables purchased in T2/T1.Psychosocial variables including beliefs, attitudes, intention, outcome expectancies and procedural knowledge measured in T2/T1.

Secondary outcome measure 3, in combination with the primary outcome measures, will allow us to calculate clinically meaningful minimum differences for a sample size calculation for a full trial.

The data collected from the loyalty cards and the questionnaires will be stored in an anonymised dataset held on servers owned and maintained by the study sponsor for a period of 15 years, after which all datasets will be deleted.

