## Methods/design

The design is a two-arm parallel randomised controlled trial comparing the intervention against information about traffic light labelling. Data collection will take place over 44 weeks, with 26 weeks of baseline data (−T1), 6 weeks of intervention (T1) and 12 weeks of follow-up without intervention (T2), with questionnaire data collected at recruitment (T0) and during the intervention (T1) and follow-up (T2) periods. Figure 2 shows how the trial will progress, and Table 2 gives a timetable for data collection.

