We are aiming to receive approximately 400 complete sets of psychosocial questionnaire data and 1200 complete sets of electronic sales data. This will allow us to detect an effect size (measured by Cohen’s d statistic) of 0.28 for the psychosocial questionnaire data and 0.16 for the electronic sales data. In general, effect sizes of 0.2 or less are considered ‘small’. The data collected in the pilot trial will allow us to refine our sample size estimates for the main trial. According to the assumed rates detailed above, we will recruit approximately 1300 participants, which will require us to email 33,000 loyalty card holders, from a total database of over 1 million. Should recruitment rates be lower than expected, further recruitment emails will be sent out.

Each of these assumed rates will be tested in the pilot trial, and the recruitment strategy may not result in the estimated number of participants. For example, it is not clear whether UK supermarket shoppers consistently use loyalty cards as much as in New Zealand, where the estimate of retention rate originates.

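### A single 12-week mean at T2 gives the average effect over follow-up; it cannot show whether the effect is sustained to week 12 and could hide a fade-out.

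*Protocol article*

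**What the plan says.** The Methods/design section sets "6 weeks of intervention (T1) and 12 weeks of follow-up without intervention (T2"). Under Outcome measures, Effect sizes, the primary outcome is summarised once per participant and period: "mean healthiness of all ready meals and pizzas purchased during the entire time period will be assessed in T-1, T1 and T2". The same paragraph says that "differences between intervention and control arms at T1 and T2 will be controlled for differences at baseline (T-1"), and that the comparison "at T2 will measure whether the effect is sustained for the following 12 weeks after the intervention is removed".

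The Statistical analysis section keeps the same two post-baseline occasions: "At time points T1 and T2, repeated measures ANCOVA will be used to assess differences between intervention and control arms". Nothing in the article splits T2, fits a trend within it or defines what would count as sustained.

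For size, the Recruitment and allocation strategy section aims for "1200 complete sets of electronic sales data" and gives detectable effects (Cohen's d) of "0.28 for the psychosocial questionnaire data and 0.16 for the electronic sales data".

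**The concern.** The summary measure and the inference drawn from it stand in the same paragraph and do not match. A mean over all of T2 answers how large the effect was on average in those 12 weeks. Whether the effect is still there towards the end is a different question, and the mean carries no information on it. More participants or narrower intervals do not help, because the limitation lies in what is being estimated.

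Fading is a realistic pattern here: the intervention is withdrawn at the end of T1, and Table 2 labels T2 as a wash-out. At stake is the persistence message taken from the pilot. A positive T2 mean could be read as a smaller but lasting effect when it came entirely from the first weeks after withdrawal.

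**Working it through.** **Inputs.** From the article: T1 of 6 weeks, T2 of 12 weeks, one mean per participant and period, N = 1200 for sales data, detectable d of 0.16 (sales) and 0.28 (questionnaire, N = 400). Assumed, because the article does not state them: 1:1 allocation, two-sided 5%, 80% power, purchases spread evenly over T2. Effects are in units of the SD of the 12-week mean.

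**Step 1: reproduce the article's figures.** With unit SD and equal arms, SE = sqrt(4/N) and detectable d = (1.960 + 0.842) × SE.
- N = 400: SE = 0.100, d = 0.280 (article: 0.28).
- N = 1200: SE = 0.0577, d = 0.162 (article: 0.16; power at exactly 0.16 is 79%).

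Both agree, so the assumed power, test level and allocation are consistent with the article's calculation.

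**Step 2: what the T2 mean returns.** Let the initial effect be δ.
- Constant half effect: (12 × 0.5δ)/12 = 0.5δ.
- Full for weeks 1-6, then none: (6 × δ + 6 × 0)/12 = 0.5δ.
- Straight-line fall from δ to 0: (δ + 0)/2 = 0.5δ.

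The planned contrast has the same expected value under all three, although the effect at week 12 is 0.5δ in the first and zero in the other two.

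**Step 3: how often a vanished effect still gives a significant T2 contrast.** Chance = Φ(0.5δ/0.0577 − 1.96).

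| Initial effect δ | T2 mean contrast | Chance of significance |
|---|---|---|
| 0.16 | 0.08 | 28% |
| 0.20 | 0.10 | 41% |
| 0.24 | 0.12 | 55% |
| 0.28 | 0.14 | 68% |
| 0.32 | 0.16 | 79% |
| 0.40 | 0.20 | 93% |

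If 40% to 70% of T2 purchases fall in weeks 1-6 instead of half, the chance runs from 20% to 49% for δ = 0.16 and from 60% to 97% for δ = 0.32.

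**Step 4: precision if T2 is halved.** Let ρ be the correlation between a participant's two half-period means; the article gives no value, so 0.3 to 0.9 is assumed. Setting the SD of the 12-week mean to 1 gives s²(1 + ρ)/2 = 1, so each half has SD s = sqrt(2/(1 + ρ)), and the detectable d for one half is 0.162 × s.
- ρ = 0.3: s = 1.240, d = 0.201.
- ρ = 0.5: s = 1.155, d = 0.187.
- ρ = 0.7: s = 1.085, d = 0.175.
- ρ = 0.9: s = 1.026, d = 0.166.

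The comparison is 0.162 for the full 12 weeks. In the scenario of step 3, the weeks 7-12 contrast would be significant only at the 5% false-positive rate.

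**The case against.** The strongest reply is that this is loose wording in a pilot. The average effect over 12 weeks after withdrawal is a valid randomised contrast, the plan reports estimates with 95% confidence intervals, and the article warns that power is not guaranteed. T1 and T2 are both estimated, so a T2 effect half the size of the T1 effect would itself hint at fading. Finer time windows could be left to an analysis plan. Nearly all of this stands. It does not make the sentence about a sustained effect true, because a halved estimate does not tell a lasting half effect from one that has gone by week 12.

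A reader might infer more than the article supports:
- *That an effect vanishing halfway would be reported as lasting.* No rule equates a significant T2 contrast with a sustained effect, and at the article's own detectable effect of 0.16 a non-significant T2 result is the likelier one (about 72%). The 79% figure needs an initial effect twice that size.
- *That the main trial would be given a wrong effect size.* If it keeps the same outcome, the pilot's T2 mean and SD are the right inputs.
- *That early T2 purchases are contaminated by T1, or that unequal period lengths bias the contrasts.* An effect continuing after withdrawal is what persistence means. The outcome is a mean score per item, so period length by itself changes precision and does not bias either contrast.
- *That persistence is the only purpose of T2.* T2 also serves retention, questionnaire completion and the secondary outcomes.

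One further objection to the remedy stands: a weeks 7-12 mean is again an average, and an effect ending at week 9 would still show in it. The split narrows the problem without removing it.

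**Conclusion.** The point holds in limited form. The planned T2 contrast estimates the average effect over 12 weeks and cannot support a statement that the effect was sustained for 12 weeks. This follows from the outcome definition and needs no numerical assumption.

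How often it would mislead depends on the initial effect: under the drop-at-week-6 pattern, a significant T2 contrast is unlikely at 0.16 SD, about an even chance at 0.24 and likely at 0.32. Those figures rest on the assumed allocation, test level and even purchasing, and on treating the initial effect as expressed in the SD of the 12-week mean, which need not equal that of the 6-week T1 mean. It is a worthwhile and cheap improvement; the randomised comparison itself remains valid.

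**What to change.** Keep the 12-week mean and describe it as the average effect over T2. Add arm contrasts with 95% confidence intervals for T2 weeks 1-6 and weeks 7-12, or an arm-by-time term within T2, with the same baseline adjustment. Rest any statement about persistence on the later window, worded as the average over weeks 7-12. At the least, reword the sentence in Effect sizes so that it claims only an average.

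No new data should be needed: the sales data cover all food purchases in the study period, and censoring at the withdrawal date (Consent section) implies dated records.

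The cost is somewhat wider intervals, with a detectable d of about 0.17 to 0.20 per half against 0.16 for the whole period (assumed correlations of 0.9 to 0.3). Some participants will also have no ready meal or pizza purchase in a half and so no score for it; their number should be reported by arm.
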